### Follow-up evaluation, assessment of efficacy, and data collection

Patients will be seen at 1 and 3 months after SRT and every 3 months thereafter. At each visit, physical examination, KPS, JCS, toxicities, and MRI of the brain are evaluated. MMSE is evaluated every 6 months after SRT. Since poorly timed MRI may be required depending on symptom, the time of MRI at plus or minus 1 month is allowed. The adverse events will be evaluated using CTCAE ver. 5.0. Table 1 shows the follow-up schedule. After progression at an intracranial site, additional treatment (e.g., WBRT) is at the discretion of the radiation oncologists. Anonymized data will be transmitted to the principal investigator from participating centres via the case reporting form. Anonymized data will be collected before SRT (baseline) and at 1 and 3 months after SRT and every 3 months thereafter according to Table 1. When any treatment-related death, any Grade 4 toxicity, and any death during the SRT periods or within 30 days of SRT is observed, the toxicity reporting form will be transmitted to the principal investigator from participating centres.

**Table 1 Tab1:** Pre- and post-treatment evaluation and assessment of efficacy

	Baseline	Treatment	Follow-up after				
Assessment^a^			1 M	3 M	6 M	Every 3 M thereafter	Every 6 M thereafter
Medical history	✓						
Physical examination	✓		✓	✓	✓	✓	
CT or PET-CT^b^	✓						
KPS	✓		✓	✓	✓	✓	
JCS	✓		✓	✓	✓	✓	
MMSE	✓				✓		✓
Brain MRI	✓		✓	✓	✓	✓	
Adverse events		✓	✓	✓	✓	✓	

Footnotes: *M* Months, *CT* Computed tomography, *PET-CT*
^18^F-fluorodeoxyglucose positron emission tomography-computed tomography, *KPS* Karnofsky performance status, *JCS* Japan Coma Scale, *MMSE* Mini mental status examination, *MRI* Magnetic resonance imaging

^a^Extra imaging outside of the study schedule is allowed per the discretion of the physician

^b^Either enhanced CT or PET-CT is required

## Statistical analysis

### Randomization

The study will employ a 1:1 randomization between Arm 1 (consecutive daily irradiation) and Arm 2 (irradiation at two- to three-day intervals), based on the stratification factors described in the Design section. Random assignment of treatment groups is centrally managed by [name] using the web-based system of Mujinwari (Iruka System Ltd., Tokyo, Japan) and is balanced with randomly permuted blocks. [name] is a member of data managing team and is not involved in enrollment. The other co-investigators are responsible for enrollment. Interventions will be initiated within 14 days of randomization.

### Sample size

We use a randomized phase II screening design, with a two-sided α of 0.20 and a power of 80% as recommended for our current study [12]. In a phase II screening design, the α level is set higher than the level of a phase III design (i.e., 0.05). Even if the phase II trial is positive (i.e., *p* < 0.20), that is not considered conclusive without a subsequent phase III trial. The results of the previous study of irradiation at intervals demonstrated a 1-year IC-LC of 93% [13]. Assuming a 1-year IC-LC of 70% for Arm 1 (consecutive daily irradiation) and 90% for Arm 2 (irradiation at two- to three-day intervals) and a 1-year OS of 50% for target patients, with 80% power, alpha of 0.20, an 5% lost follow-up rate, accrual time of 4 years and a total trial time of 5 years, 70 patients will be required (35 in Arm 1 and 35 in Arm 2). The secretariat of the study will contact all co-investigators to facilitate enrollment regularly.

### Primary endpoint

The intention-to-treat analyses will be performed, and patients will be analyzed in the groups to which they are assigned. The IC-LC rate will be calculated using the Kaplan-Meier method and differences will be compared using the stratified log-rank test. Only recurrence of initially treated sites will be treated as event and death will not be considered to be competing event. When enrolled patient dies, the data at the last follow up will be used to calculate the IC-LC rate. Cox proportional hazards multivariable regression analysis will be used to determine baseline factors predictive of primary endpoint.

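### The Kaplan-Meier IC-LC rate censors deaths, so read as patient risk it overstates local failure and the percentage-point difference between arms; the log-rank comparison is sound

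*Protocol article*

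**What the plan says.** In the protocol article, the Primary endpoint section under Statistical analysis has the IC-LC rate estimated by Kaplan-Meier and the arms compared by a stratified log-rank test. On death it says: "Only recurrence of initially treated sites will be treated as event and death will not be considered to be competing event". It adds: "When enrolled patient dies, the data at the last follow up will be used to calculate the IC-LC rate". Patients who die without local recurrence are therefore censored.

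The Sample size section gives the planning values: "Assuming a 1-year IC-LC of 70% for Arm 1 (consecutive daily irradiation) and 90% for Arm 2", together with "a 1-year OS of 50% for target patients". The design is set "with a two-sided α of 0.20 and a power of 80% as recommended for our current study", and the result is that "70 patients will be required (35 in Arm 1 and 35 in Arm 2"). The trial is positive if p < 0.20.

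The article mentions no cumulative-incidence estimate and does not describe the Kaplan-Meier rate as net of death.

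**The concern.** A patient who has died can no longer have a local recurrence, so death competes with the endpoint whatever the plan calls it. Kaplan-Meier with deaths censored lets each dead patient be represented by those still alive and at risk. What it estimates is control in a hypothetical population without death. That is a legitimate quantity, but it is not the share of randomised patients whose treated lesions stay controlled or recur.

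With few deaths the two nearly coincide. Here the plan itself expects 50% mortality at 1 year, so they separate. The primary endpoint is named as a rate, and the article says that a positive result would still need a phase III trial. The absolute rates are therefore likely to be quoted, used in counselling patients and taken into later planning. Read as patient risks, they would be too high, and so would the gap between the arms.

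**Working it through.** **Inputs** (Sample size section): 1-year IC-LC 70% and 90%; 1-year overall survival 50%; two-sided alpha 0.20; power 80%; "an 5% lost follow-up rate"; "accrual time of 4 years and a total trial time of 5 years".

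**Added assumptions:** constant hazards, the same mortality in both arms, death independent of local failure, uniform accrual.

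**Hazards per year**
- Local failure, Arm 1: l1 = -ln 0.70 = 0.357
- Local failure, Arm 2: l2 = -ln 0.90 = 0.105
- Death: m = -ln 0.50 = 0.693
- Hazard ratio: 0.105/0.357 = 0.295

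**Step 1: the plan's own figure.** With s = l + m, 4 years of accrual and 5 years in total, the probability of an observed local failure with deaths censored is (l/s) × [1 − (e^(−s) − e^(−5s))/(4s)].
- Arm 1: 0.312. Arm 2: 0.114. Mean 0.213, so about 14.9 events in 70 patients.
- Total N before any allowance for loss: 57 (Schoenfeld), 70 (Lachin-Foulkes), 72 (Freedman), 73 (Rubinstein).
- Dividing by 0.95 for loss: 60, 74, 76 and 77.
- Leaving deaths out altogether, Lachin-Foulkes would need only about 33.
- Simulated power of an unstratified log-rank test (20,000 runs): 82.7% with 35 per arm, 80.9% with 33 per arm (about 5% lost).

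The article does not name its formula, but 70 patients is consistent with a log-rank design that already allows for the deaths.

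**Step 2: what happens to patients by 1 year.** Cumulative incidence of local failure is CIF(1) = l/(l+m) × (1 − e^(−(l+m))).
- Arm 1: 0.357/1.050 × (1 − 0.70 × 0.50) = 0.3397 × 0.65 = 22.1%
- Arm 2: 0.105/0.799 × (1 − 0.90 × 0.50) = 0.1319 × 0.55 = 7.3%

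| At 1 year | Arm 1 | Arm 2 | Difference | Ratio |
|---|---|---|---|---|
| One minus Kaplan-Meier | 30.0% | 10.0% | 20.0 points | 3.00 |
| Cumulative incidence | 22.1% | 7.3% | 14.8 points | 3.04 |
| Excess | 7.9 points | 2.7 points | 5.2 points | |

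As a check, Arm 1 at 1 year splits into 22.1% with local failure, 42.9% dead without it and 35.0% alive and controlled, which sum to 100%. For 35 patients all followed to 1 year, that is 0.221 × 35 = 7.7 expected local failures, where 30% would suggest 10.5.

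**Step 3: sensitivity to the survival assumption**

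| 1-year survival | CIF Arm 1 | CIF Arm 2 | Difference |
|---|---|---|---|
| 70% | 25.5% | 8.4% | 17.1 points |
| 50% | 22.1% | 7.3% | 14.8 points |
| 30% | 18.1% | 5.9% | 12.2 points |

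**Step 4: the deciding test.** With equal local-failure hazards, the simulated log-rank test with deaths censored rejects in 20.2% to 20.3% of runs at a nominal 20%. If mortality also differs between arms (death hazard ratio 0.7, assumed), it still rejects in 20.2%, while a Gray-type test rejects in 23.7%. Under the planned effect the Gray-type test has 79.5% power, against 82.7% for the log-rank.

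**The case against.** The strongest reply is that the rule is explicit, prespecified and suited to the question. The trial asks whether longer intervals between fractions improve control of the treated lesion. For that, the cause-specific hazard is a defensible target, and a net control rate goes naturally with it. The article never says that IC-LC is the proportion of patients who fail. This stands. It is why the Kaplan-Meier curve can stay and why the test should not be replaced; Step 4 shows that a Gray-type test would respond to a mortality difference alone.

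Three stronger readings are tempting, and the documents do not support them.

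- **A reader might infer that the positive or negative call is compromised.** It is not. It rests on the log-rank p-value, which keeps its level, and the sample size already allows for the deaths.
- **A reader might infer that the effect carried to phase III would be wrong.** That holds only if percentage-point differences are carried forward as patient risks. A log-rank phase III sized on hazards plus a death hazard, as this trial appears to be, would not be misled. Putting the cumulative-incidence percentages into such a calculation would count death twice.
- **A reader might infer that control is credited in unimaged time.** The Follow-up evaluation section and Table 1 schedule a brain MRI at every follow-up visit, so the last follow-up will usually carry an MRI. The wording does not tie the two together, which leaves a small ambiguity and no more.

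The objection does not answer that the rate is unlabelled, and that the text denies competition from death while planning for 50% mortality.

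**Conclusion.** The point holds for the absolute rates. On the plan's inputs, one minus Kaplan-Meier at 1 year exceeds the actual probability of local failure by 7.9 points in Arm 1 and 2.7 points in Arm 2. The arm difference reads as 20.0 points instead of 14.8, so about a quarter of it (5.2/20.0) is not present as a difference in patient risk.

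The direction does not depend on the exact mortality: across 1-year survival of 70% to 30% the cumulative-incidence difference stays below 20 points. The size depends on constant hazards, equal mortality by arm and death being independent of local failure. The 50% survival is a planning assumption, not an observed value.

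Relative measures are not inflated: the hazard ratio stays at 0.295, and the ratio of 1-year failure rates is 3.00 by one approach and 3.04 by the other. This is a matter of estimation and reporting that should be put right, not a flaw in the trial's decision rule.

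**What to change.** - Keep the stratified log-rank test as the primary test and describe it as a comparison of the cause-specific hazard of local recurrence, with deaths censored. Alpha and N stay as they are.
- Delete the statement that death is not a competing event.
- Report the Aalen-Johansen cumulative incidence of local failure by arm, with confidence intervals and death as the competing event, beside the Kaplan-Meier curve.
- Label the Kaplan-Meier IC-LC rate as net of death.
- As a minor clarification, define the last follow-up used for censoring as the last evaluable brain MRI.

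The cost is a few words in the analysis section and one routine estimate; the death dates are already needed for overall survival. The downside for the sponsor is a smaller reported absolute difference, about 15 points in place of 20 under the planning assumptions.

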### Secondary endpoints

The IC-PFS rate will be calculated using the Kaplan-Meier method and differences will be compared using the stratified log-rank test. Only development of initially treated sites and new BM will be treated as event and death will not be considered to be competing event. When enrolled patient dies, the data at the last follow up will be used to calculate the IC-PFS rate. The OS rate will be calculated using the Kaplan-Meier method and differences will be compared using the stratified log-rank test. OS was defined as the time from the date of randomization to death from any cause.

The rates of grade 2 or higher toxicity will be compared between groups using the Fisher’s Exact Test. The non-worsening of KPS and MMSE scores at 6- and 12-months post-enrollment will be measured with differences between groups tested using the Fisher’s Exact Test. When enrolled patient dies, the data at the last follow up will be used. For KPS, a decrease in KPS of ≥10% will be considered a decline in KPS and sensitivity analysis will be performed. For MMSE, a decrease in MMSE score of ≥3 points will be considered a decline in cognitive function and sensitivity analysis will be performed.

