### Secondary endpoints

Intracranial progression-free survival (IC-PFS), defined as intracranial PFS at initially treated and at new sites.OS, defined as the time from the date of randomization to death from any cause.Toxicity, assessed by the National Cancer Institute Common Terminology Criteria for Adverse Events (CTCAE) version 5.0.Non-worsening of Karnofsky performance status (KPS), defined as the time from randomization to decline of KPS from any cause.Non-worsening of mini mental status examination (MMSE), defined as the time from randomization to decline of MMSE from any cause.

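### IC-PFS is named progression-free survival but censors deaths, so its Kaplan-Meier rate is a death-censored time to intracranial progression and can exceed OS (secondary endpoint only)

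*Protocol article*

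**What the plan says.** The list of secondary endpoints under Methods/design gives "Intracranial progression-free survival (IC-PFS), defined as intracranial PFS at initially treated and at new sites". That wording repeats the term it defines: it names the sites that count and does not mention death.

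The event rule comes under Statistical analysis, Secondary endpoints: "Only development of initially treated sites and new BM will be treated as event and death will not be considered to be competing event". The next sentence covers deaths: "When enrolled patient dies, the data at the last follow up will be used to calculate the IC-PFS rate". The estimator and test are also fixed there: "The IC-PFS rate will be calculated using the Kaplan-Meier method and differences will be compared using the stratified log-rank test".

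For OS, the same section counts every death: "OS was defined as the time from the date of randomization to death from any cause". The Sample size section assumes "a 1-year OS of 50% for target patients". No part of the article makes death an IC-PFS event.

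**The concern.** A progression-free survival rate is the proportion of patients alive and without progression, so it cannot be higher than the proportion alive. The rule in the analysis section estimates something else: how long patients would remain free of intracranial progression if those who died could still progress later at the same rate as those still followed. Both quantities are legitimate, but they need different names.

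The difference is not marginal here, because the plan expects half the patients to have died by one year. A reader who takes the label at face value would read the published figure as the chance of being alive with a controlled brain. A reader who recognises it as time to progression would still be misled if one minus the curve were taken as the proportion of patients who progress.

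**Working it through.** **The plan's own figure.** The article gives no figure for IC-PFS; its only calculation is N = 70 for the primary endpoint. I reproduced that first, to see how the plan itself treats death.

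- Inputs (Sample size section): 1-year IC-LC 70% and 90%, 1-year OS 50%, two-sided alpha 0.20, power 80%, accrual 4 years, total 5 years, 5% loss.
- Hazards per year: h1 = -ln 0.70 = 0.357; h2 = -ln 0.90 = 0.105; mean 0.231; death -ln 0.50 = 0.693.
- With uniform accrual and death as censoring, the probability of an observed event is 0.312 in Arm 1, 0.114 in Arm 2 and 0.224 at the mean hazard.
- N = [1.282 × √(4 × 0.231² / 0.224) + 0.842 × √(2 × 0.357² / 0.312 + 2 × 0.105² / 0.114)]² / (0.357 - 0.105)² = 69.7 (computed without rounding).
- With the 5% loss spread over five years, N = 70.3.

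So 70 reproduces with death as censoring. Dividing by 0.95 instead gives 73.3, so the match depends on how loss is handled. IC-PFS does not enter this calculation.

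**What the IC-PFS rule estimates.** Let KM be the death-censored Kaplan-Meier value at one year. If death and progression are independent, then

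true PFS = KM × OS = KM × 0.50.

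The ratio KM / PFS is 1 / 0.50 = 2, whatever the progression rate. With constant hazards, where hp = -ln KM and hd = 0.693, the actual probability of intracranial progression by one year is

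cumulative incidence = hp / (hp + hd) × (1 - PFS).

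For KM = 60%: hp = 0.511, PFS = 0.30, and cumulative incidence = 0.511 / 1.204 × 0.70 = 0.297.

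The article gives no rate of intracranial progression or of new metastases, so the first column below is assumed.

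| Death-censored KM (assumed) | True PFS | 1 - KM | Cumulative incidence of progression |
|---|---|---|---|
| 40% | 20% | 60% | 45.5% |
| 50% | 25% | 50% | 37.5% |
| 60% | 30% | 40% | 29.7% |
| 70% | 35% | 30% | 22.1% |

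A simulation of 200,000 patients per row agreed. At an assumed 60% it gave a death-censored KM of 0.600, PFS of 0.301 and OS of 0.501.

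**Can the rate exceed OS?** The sample size section supplies part of the answer: "Assuming a 1-year IC-LC of 70% for Arm 1 (consecutive daily irradiation) and 90% for Arm 2". If local recurrence and new metastases are independent, the death-censored rate is IC-LC × freedom from new metastases. It passes 50% when one-year freedom from new metastases is above 0.50 / 0.70 = 71% in Arm 1, or above 0.50 / 0.90 = 56% in Arm 2. A true PFS could not pass 50% under any assumption about dependence.

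**The case against.** The strongest reply is that the rule is openly stated, that the endpoint list defines IC-PFS by site without promising to count deaths, and that OS is analysed separately. A log-rank test that censors deaths is also a valid comparison of cause-specific hazards, and arguably the relevant one for a hypothesis about fractionation interval and tumour control.

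Most of this stands. The test is sound for that question, and disclosure means that the analysis itself is not ambiguous. But disclosure in the methods does not make the name right, and a PFS cannot be rebuilt from separate progression and OS curves without assuming independence. The primary endpoint uses the same censoring, but it is called a local control rate, which does not include survival by name.

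Some stronger readings are tempting, and the article does not support them:

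- **The trial's conclusion is at risk.** IC-PFS is one of five secondary endpoints. Alpha, power, N = 70 and the p < 0.20 criterion all rest on IC-LC.
- **The reported rate will exceed OS, or will be far too high.** The new-metastasis rate is not given, so only *can exceed* is supported. The rate is too high only when read as a PFS, and the factor of two comes from independence and the planned OS.
- **A difference in deaths between arms would be missed.** This curve would miss it, but the OS analysis has its own Kaplan-Meier estimate and stratified log-rank test.
- **The result cannot be compared with other trials.** That depends on how other trials define the endpoint, which the article does not show.

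**Conclusion.** The point holds as a fault in a secondary endpoint. Followed exactly, the plan would report a death-censored time to intracranial progression under the name progression-free survival. That conclusion rests on the text alone, reading the use of last follow-up data after a death as censoring.

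The size rests on assumptions. With 1-year OS of 50% and independence, the figure is about twice the true 1-year PFS (20-30% for an assumed 40-60%). One minus the curve overstates the probability of progression, for example 40% against about 30%; this second figure also uses constant hazards. If intracranial progression itself raises the risk of death, deaths among progression-free patients are fewer than OS implies and the factor is below two. The ceiling at OS for a true PFS needs no such assumption. The calculation censors at the date of death; the plan's last follow-up would fall somewhat earlier.

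It should be corrected before analysis, but it does not threaten the trial's validity.

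**What to change.** Either of two changes resolves it.

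(a) Define IC-PFS as time from randomization to progression at a treated site, new brain metastasis or death from any cause, whichever comes first. Keep the Kaplan-Meier estimate and the stratified log-rank test.

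(b) Rename the endpoint time to intracranial progression, report its cumulative incidence with death as a competing event, and keep the death-censored stratified log-rank test, described as a cause-specific comparison.

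Under (a) the reported rate is lower and an effect confined to intracranial progression is diluted by deaths. As an illustration with assumed values, take a death-censored 1-year rate of 40% in the control arm, a progression hazard ratio of 0.5 and 1-year OS of 50% in both arms. The PFS hazard ratio is then (0.458 + 0.693) / (0.916 + 0.693) = 0.72. Under (b) that dilution is avoided, but the trial no longer reports a PFS. The choice depends on which question the investigators want this endpoint to answer.

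Either change takes a few sentences in the endpoint and analysis sections, plus the notice to hospitals, IRBs and registries that the protocol requires for amendments. No new data or patients are needed, because deaths are already collected for OS. The Trial status section puts the end of data collection at March 2027, and the change should be fixed before the analysis.

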### Study design

The study is conducted as a multicenter open-label randomized control phase II trial. Patients will be randomized in a 1:1 ratio between consecutive irradiation (Arm 1) vs. irradiation at intervals (Arm 2) to BM. Patients will be stratified by (1) maximum diameter (≤ 2 cm vs. > 2 cm) among their BM and (2) number of BM (1, 2 vs. 3-5). Figure 2 shows the study schema.

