### Pre-treatment evaluation

Re-staging is performed within 8 weeks prior to randomization. ^18^F-fluorodeoxyglucose (18-FDG) positron emission tomography (PET) -computed tomography (CT) or a contrast-enhanced CT of the neck to the pelvis is recommended for the evaluation of extracranial metastases. In cases where a contrast agent is unavailable due to impaired renal function or allergic intolerance, a plain CT is allowed. Before random assignment within 2 weeks, all patients are necessary to be evaluated by an MRI of the brain. MRI is performed with a gadolinium-enhanced T1 3D Fast Field Echo and 3D reconstruction of the axial, sagittal, and coronal planes with 1 mm slice thickness (thin-slice MRI). In addition, each patient undergoes a baseline evaluation consisted of medical history including prior treatments of cancer and concomitant anticancer medications, symptom burden, KPS, Japan Coma Scale (JCS), and MMSE.

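### The OS test is valid but ignores baseline KPS and extracranial disease; adjusting for both could add a modest amount of power, depending on how prognostic they are

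*Protocol article*

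**What the plan says.** The second Secondary endpoints section, under Statistical analysis, fixes the OS comparison: "The OS rate will be calculated using the Kaplan-Meier method and differences will be compared using the stratified log-rank test". OS runs from randomization to death from any cause.

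The strata come from Study design: "Patients will be stratified by (1) maximum diameter (≤ 2 cm vs. > 2 cm) among their BM and (2) number of BM (1, 2" against 3 to 5). The Randomization section uses the same factors, "based on the stratification factors described in the Design section". Both describe the lesions in the brain.

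Two patient-level characteristics are assessed at baseline. Pre-treatment evaluation lists "symptom burden, KPS, Japan Coma Scale (JCS), and MMSE". For disease outside the brain, PET-CT or a "contrast-enhanced CT of the neck to the pelvis is recommended for the evaluation of extracranial metastases", while the Table 1 footnote is firmer: "Either enhanced CT or PET-CT is required".

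The article names a multivariable Cox model only for the primary endpoint, intracranial local control (IC-LC), and only to look for predictive baseline factors. It states no covariate-adjusted comparison for OS.

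**The concern.** When covariates that predict death are left out of a proportional-hazards comparison, the estimated treatment effect is pulled toward the null and power falls. The OS test conditions on lesion size and number only, although it counts deaths from any cause, and two candidate predictors are already being assessed.

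The one multivariable model in the article is attached to the endpoint with few events, while OS, with far more, has none. The article promises an assessment of the interval's impact on survival, so the OS estimate will be read. If covariates are chosen only after the data are seen, an adjusted OS result will carry little weight.

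**Working it through.** **1. The plan's own figure.** No effect size, power or event count is given for OS. The only figure is 70 patients, set for IC-LC (70% vs 90% at 1 year, 1-year OS 50%, two-sided alpha 0.20, power 80%, 5% loss, 4 years' accrual, 5 years in total).
- IC-LC hazard ratio: ln 0.9 / ln 0.7 = 0.295.
- With death as censoring, the mean event probability is 0.213.
- Schoenfeld's formula needs 12.1 events. Taking 14 (7 per arm): 14 / 0.213 = 65.7, and 65.7 / 0.95 = 69.2, so 70. The figure is reproduced. Other standard variants run from about 62 to 80.
- Expected IC-LC events: 70 × 0.95 × 0.213 = 14.2.

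**2. Expected deaths.** Death hazard λ = ln 2 = 0.693. Reading the 5% loss as annual (an assumption), μ = −ln 0.95 = 0.051. For follow-up uniform on 1 to 5 years:

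P(death) = λ/(λ+μ) × [1 − (e^−(λ+μ) − e^−5(λ+μ)) / (4(λ+μ))]

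- No difference between arms: 0.931 × (1 − 0.151) = 0.790, and 70 × 0.790 = 55 deaths.
- With the calendar dates in Trial status (3.5 years' accrual, 4.5 in total): 0.774 × 70 = 54.
- If one arm has OS hazard ratio 0.6 (λ = 0.416): 0.890 × (1 − 0.284) = 0.638. The average is (0.790 + 0.638)/2 = 0.714, and 70 × 0.714 = 50 deaths.

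Treatment plus two covariates is three parameters: 50/3, or about 17 deaths per parameter.

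**3. Unadjusted power at 50 deaths, two-sided 0.20.** Φ(√D/2 × |ln HR| − 1.282):
- HR 0.7: Φ(3.536 × 0.357 − 1.282) = 49%
- HR 0.6: Φ(3.536 × 0.511 − 1.282) = 70%
- HR 0.5: Φ(3.536 × 0.693 − 1.282) = 88%

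**4. Gain from adjustment.** This was simulated with 70 patients, 3,000 trials per setting, OS hazard ratio 0.6 and two-sided 0.20. The stratified log-rank test is compared with a stratified Cox model that adds KPS and extracranial disease (EC). All prognostic strengths and prevalences are assumptions.

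| Assumed hazard ratios for death | Log-rank % | Adjusted % | Gain |
|---|---|---|---|
| Weak: 1.3 and 1.3, each in 50% | 65.0 | 65.3 | 0.3 |
| Weak: KPS 1.5 (30%), EC 1.3 (70%) | 66.2 | 66.7 | 0.5 |
| Weak: EC 1.5, KPS 1.2 per 10 points | 66.0 | 68.1 | 2.1 |
| In between: KPS 2 (30%), EC 1.5 (70%) | 62.2 | 64.2 | 2.0 |
| Moderate: KPS 2 (30%), EC 2 (70%) | 60.7 | 64.3 | 3.6 |
| Moderate: 2 and 2, each in 50% | 58.7 | 64.3 | 5.6 |
| Moderate: EC 2.0, KPS 1.4 per 10 points | 63.9 | 70.0 | 6.1 |
| Strong: EC 2.5, KPS 1.6 per 10 points | 58.2 | 67.2 | 9.0 |

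Rows with KPS per 10 points assume EC in 60% and KPS 70/80/90/100 in 20/25/35/20%. The other rows treat both factors as binary. Monte Carlo error is about 0.9 point on each power, so gains of a point or less amount to nothing.

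**5. Is the gain only type I error?** At the 0.05 level, type I error was 4.9 to 5.8% adjusted against 4.8 to 5.0% planned. By normal approximation, moving from 5.0% to 5.8% at 40.5% power adds about (1.960 − 1.896) × 0.388 = 2.5 points, as much as the whole weak-factor gain at that level (40.5 to 42.7%). A separate simulation at 0.20, corrected for size, still gave about 1 point for weak factors, 4 for moderate and 5 for strong. It showed a loss of up to 2 points when neither factor was prognostic.

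**The case against.** The strongest reply is that nothing here is wrong. A log-rank test stratified by the randomization factors is valid and matches the randomization. OS is secondary and has no power target. An adjusted model for a secondary endpoint is often left to an analysis plan, which is not shown. This largely stands. It makes the point an improvement rather than a correction, and the point closes if the analysis plan already contains such a model. What remains is that the article does state the OS method, and names a multivariable model for IC-LC only.

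A second reply is that the documents nowhere say that KPS or extracranial disease predicts death in these patients, or how strongly. That stands too. KPS of at least 70 at entry also narrows the KPS contrast. The strong setting implies 1.6³ = 4.1-fold hazard across KPS 70 to 100, and 4.1 × 2.5, about 10-fold, combined, so it is an outer edge.

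A reader might infer three stronger things that the documents do not support:
- **That the plan forfeits a fixed 2 to 10 points of power.** The lower end vanishes with weak or null factors. The upper end (30.8 to 41.1%) comes from a two-sided 0.05 level, while the only level the article sets is 0.20.
- **That chance imbalance makes the OS test invalid.** If 60% have a factor, a gap of at least 5 patients between arms of 35 has probability about 27%, and of at least 7 about 11%. The test's type I error already allows for this, as the 4.8 to 5.0% above shows. Adjustment sharpens the estimate; it does not repair the test.
- **That extracranial status is ready to use.** The article lists the imaging, recommended in one place and required in another, with plain CT allowed in some cases. It does not show a coded yes/no item.

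**Conclusion.** The point holds as a missed efficiency gain of low severity. The OS test is sound, but it leaves unused two baseline characteristics that the trial assesses, on an endpoint with enough deaths (about 50 to 55) to carry them.

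Taking the uncorrected and size-corrected results together, at an assumed OS hazard ratio of 0.6 and two-sided 0.20, the gain is about 0 to 2 points for weak factors, 4 to 6 for moderate and 5 to 9 for strong. If neither predicts death, there is no gain, or a loss of up to about 2 points. The direction is secure only if the factors are prognostic; the size rests on assumed strengths, prevalences and OS effect. No conclusion about IC-LC, and nothing in the sample size, depends on this.

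**What to change.** Prespecify for OS a Cox model stratified by the two randomization factors, with treatment, baseline KPS as a score and extracranial metastases (yes/no) as covariates. Report it with the Kaplan-Meier curves and the stratified log-rank test. State before the data are analysed which result is the main one; listing the model as a prespecified supportive analysis would still secure most of the benefit.

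Two preparations are needed. Confirm that extracranial status is a coded case-report-form item, and reconcile the recommended and required wording for the baseline imaging. Also reconcile the diameter strata: the abstract puts a lesion of exactly 2 cm in the upper stratum and Study design puts it in the lower, which affects any stratified analysis.

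Keep the stratified form. An unstratified Cox model with all four factors showed gains of about 4 to 11 points, but about 2 of these came from a type I error near 22% instead of 20%.

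The cost is a few lines of analysis text, minor programming and possibly one form item. The downsides are a type I error that may rise by up to about 1 point, and a hazard ratio that is conditional on the covariates and must be described as such.
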